## Abstract

**Background:**

Treatment of Parkinson's disease (PD) is symptomatic and frequently consists of complicated medication regimes. This negatively influences therapy adherence, resulting in lower benefit of treatment, drug related problems and decreased quality of life (QoL). A potential effective intervention strategy is a structured medication review, executed by community pharmacists. However, little is known about the effects on clinical endpoints like QoL, as well as on feasibility and cost-effectiveness in PD patients.

**Objectives:**

To assess the effect of a structured medication review on QoL in PD patients. Secondary objectives are measurements of physical disability, activities in daily life, non-motor symptoms, health state, personal carers' QoL and cost-effectiveness. Furthermore, a better insight in the process of performing medication reviews will be obtained from the perspective of community pharmacists.

**Methods:**

In this multicenter randomized controlled trial we aim to enroll 200 PD patients from the outpatient clinic of three Dutch hospitals. Community pharmacists will perform a structured medication review in half of the assigned patients; the other half will receive usual care. Data obtained by use of six validated questionnaires will be collected at baseline and after 3 and 6 months of follow-up. Semi-structured interviews with community pharmacists will be conducted till data saturation has been reached.

**Discussion:**

This trial targets a high-risk patient group for whom optimizing therapy by a structured medication review might be of added value. If effectiveness is proven, this could further promote the implementation of pharmaceutical care in a primary care setting.

## Introduction

1

Parkinson's disease (PD) is a progressive, neurodegenerative and age-related disease, affecting approximately 7.5 million patients worldwide. Because of the aging population, this is expected to increase up to more than 9 million in 2030 [1,2].

Most of the PD symptoms result from degeneration of dopaminergic neurons within the substantia nigra, leading to a shortage of dopamine in the striatum [3]. Clinical characteristics are tremor, rigidity, bradykinesia and postural instability [4,5]. Other non-motor symptoms, both dopaminergic and non-dopaminergic, include progressive cognitive and autonomic dysfunction. PD symptoms contribute to the reduction of functional abilities, shortened life expectancy and reduced quality of life (QoL) [[6], [7], [8]]. The clinical signs occur across all PD stages, but become increasingly prevalent as the disease progresses.

To date, drug treatment is the mainstay for its management [9,10]. However, the effectiveness of long-term treatment is known to decrease, leading to end-of-dose deterioration, fluctuations in medication response and side-effects [11,12]. When the disease progresses and the therapeutic window narrows, dosing frequency will increase and other medicines need to be added. Simultaneously, the total medication amount frequently rises due to comorbidities [13,14]. Patients often face complicated medication schedules and keeping track of it can be a challenging task [10,[15], [16], [17], [18]].

Medication adherence is an important factor towards success of treatment [19], although consistent adherence in PD is on average merely 50% [16,[20], [21], [22], [23], [24], [25], [26]]. This notably contributes to a reduced QoL and an increased burden on the healthcare system [14,15,19,20,27,28].

One of the barriers influencing compliance include complicated medication regimens with multiple daily dosing [20]. Polypharmacy easily leads to missing doses, and drug related problems (DRPs) occur [[29], [30], [31], [32], [33]].

To both improve adherence and optimize therapy, an often-recommended method and potentially effective intervention strategy is a structured medication review (SMR), defined as ‘a structured, critical examination of a patient's medicines with the objective of reaching an agreement with the patient about treatment, optimizing the impact of medicines, minimizing the number of DRPs and reducing waste’ [34].

The effects of an SMR, conducted by pharmacists, have been studied in all settings of care, where it has shown to reduce potentially inappropriate drugs [[35], [36], [37]] and to improve medication adherence, among others since customized care and shared decision-making may increase as patient preferences can be taken into account [38,39]. Furthermore, the amount of DRPs decreases [40,41]. In PD, performing an SMR may reduce the dosing frequency and complexity of medication schedules, possibly leading to simplified dosing and improved adherence [34,42], although not much is known about the effect of SMRs on clinical endpoints like QoL, which is an important parameter from a patient's perspective.

This manuscript describes a randomized controlled study assessing whether an SMR leads to improved QoL in PD patients. Additionally, measurements of daily life activities and physical disability, non-motor symptoms and personal carers' QoL will be performed. Furthermore, the feasibility and cost-effectiveness in this setting will be analyzed and a better insight in the process of performing medication reviews will be obtained from the perspective of community pharmacists.

## Methods

2

### Design

2.1

The study is designed as a multicenter randomized controlled trial (RCT) of a medication review intervention as one-time assessment in PD patients. We aim to enroll 200 patients with idiopathic PD from the neurology department of 3 Dutch hospitals (Medisch Spectrum Twente, Ziekenhuis Groep Twente and Isala hospital). Data obtained by use of validated questionnaires will be collected at baseline and after 3 and 6 months of follow-up (Fig. 1).

**Fig. 1 fig1:**
[figure not shown]
Study design flowchart.

The study will be conducted in agreement with the principles of the Helsinki Declaration and in accordance with the Medical Research involving Human Subjects Act (WMO). The research protocol is registered in the Dutch clinical trial register (NTR4500) and has been approved by the Medical Ethical Review Board Twente, the Netherlands.

### Recruitment, consent and randomization

2.2

In order to be eligible to participate, patients must meet the following criteria: (1) diagnosed with PD according to the UK-brain banking criteria [43]; (2) ≥ eighteen years of age; (3) ≥ four different medications daily; (4) ≥ four medication intake moments daily; (5) expressing motor and non-motor symptoms; (6) living (semi)-independent in the region of Enschede, Almelo, Hengelo or Zwolle; (7) be able to read and write the Dutch language. Exclusion criteria are: (1) being unable to administer their own medication, e.g. when requiring assistance from medical home care. PD patients receiving help from personal or family caregivers were not excluded based on this criterium; (2) having received a medication review within a year prior to the study; (3) having received a Deep Brain Stimulator, continuous duodopa gastro-intestinal gel therapy or continuous apomorphine therapy within a year before the study or willing to receive this within three months.

As soon as informed consent is obtained by the investigator and baseline measurements are performed, patients will be randomly assigned in a 1:1 ratio with a blinded blocked randomization with block sizes of four and eight. Inclusion is definite when patients in the intervention group complete the baseline measurements and receive an SMR, while patients in the control group only need to complete baseline measurements.

### Intervention

2.3

Community pharmacists will perform the SMR at the start of the study within the intervention group, while the control group will receive usual care and will not have a medication review during the next six months. All pharmacists are offered an accredited training regarding PD and drug treatment, the study protocol and the execution of an SMR beforehand. The latter is based on the Dutch Systematic Tool to Reduce Inappropriate Prescribing (STRIP)-method [44], a standardized tool for pharmacists for executing SMRs in Dutch patients. This method highly emphasizes the importance of involving the patient as a full partner in evaluating all medicines on drug-drug interactions, adverse reactions and problems with dosing or drug use. Possible barriers to adherence and non-adherent behavior are identified by asking questions in a non-judgmental way [45,46]. Possible interventions will be suggested, taking the patient's preferences, views and beliefs about their medicines in full account.

To ensure continuity of care and to facilitate collaboration between health care providers, clear documentation is required, for which a protocol is chosen based on the action plan for medication assessment of the Multidisciplinary guideline Polypharmacy in the Elderly and the abovementioned STRIP-method [44] (see Appendix). The protocol foresees the possibility of consulting a General Practitioner, neurologist and other specialists if necessary. Any adjustments in the medication regime will be communicated and explained to the patient.

After the review has been performed, all pharmacists record their proposed medication modifications or interventions, recommendations and possible other findings. This is sent to the collaborating health care providers. Together with the patient, the applied interventions will be evaluated within 4 months either by telephone or face-to-face.

### Outcome measures

2.4

Next to demographic characteristics, information on medication will be obtained from patients and verified by their pharmacists. Furthermore, the Rx-Risk Comorbidity Score will be calculated and used as a comorbidity measure [47]. PD severity is measured by Hoehn & Yahr (HY) stage at inclusion, based on information regarding actual HY stage as noted in the electronic patient file [48]. In case of uncertainty, a verification was asked from the treating neurologist.

#### Primary outcome

2.4.1

The primary outcome will be disease-specific quality of life, measured by the Parkinson's Disease Questionnaire-39 (PDQ-39). This validated and reliable instrument has 39 items comprising eight domains of health status: mobility, activities in daily living, emotional wellbeing, stigma, social support, cognitions, communication and physical discomfort [49,50]. It can be used to assess effectiveness of treatment, in which dimension scores are coded on a scale of 0–100 with a higher score indicating lower QoL [8]. A difference of 1.6 points in the PDQ-39 total score is required to pinpoint a clinically relevant difference or minimally important difference (MID) [51]. Depending on domain, MIDs vary between 1.8 and 11.4 points.

#### Secondary outcomes

2.4.2

Secondary objectives include activities in daily life and physical disability (AMC Linear Disability Scale (ALDS) [52]; non-motor symptoms (Non-Motor Symptoms Questionnaire (NMS-Quest) [53,54] and health status (EuroQOL-5 Dimensions-5 Levels (EQ-5D-5L, including Visual Analogue Scale (VAS) [55,56]. By using the index-based values of the EQ-5D-5L, quality adjusted life years (QALY) can be calculated, necessary for assessing the cost-effectiveness of an intervention [55]. Costs need to be taken into account to calculate these QALYs and to compare the cost-effectiveness of the SMR with other interventions in patients with PD. Costs incurred during this study are costs of medication, hospitalization, outpatient visits and home care, and the costs associated with the SMR. To assess the effects on QoL for personal or home caregivers, the PDQ-Carer questionnaire will be used [57].

All SMR forms will be collected to analyze modifications in medication regime and recommendations given to patients. This will be used descriptively.

Semi-structured, face-to-face interviews with community pharmacists will be conducted after at least one SMR has been performed by the pharmacist, to obtain insight in probable bottlenecks in the process of performing medication reviews. Interviewing will take place till data saturation has been reached.

### Sample size

2.5

Using the PDQ-39, a difference of 1.6 points in the overall score of this questionnaire is considered as clinically relevant [51]. In the current study, a difference of four points in the total score is expected to appear after intervention. A standard deviation of 15 was found in previous research [51]. This standard deviation is used to make a preliminary calculation of the sample size. Based on a significance of 5% and a power of 80%, a sample size of 198 subjects, separated into two groups of 99, is required to detect a clinically important difference between both groups. However, as the standard deviation might be different and due to the fact that the actual effect of a medication review is yet still unknown, an interim analysis will be performed after the inclusion of 2*25 patients and 3 months of follow up. This estimate will provide a more appropriate basis to determine the final sample size.

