### Data analysis

2.7

Between-group differences in categorical variables will be analyzed using a Chi-square test or Fisher's exact test, as appropriate, while continuous variables will be analyzed using t-tests or a Mann-Whitney test, as appropriate. Continuous data will be presented as means with standard deviations (SD) in case of normal distributions or as medians with interquartile ranges (IQR) in non-normal distributions. For all continuous variables, a repeated measurement analysis will be performed to deal with possible missing data. According to the PDQ-39 manual, missing data will be imputed using Expectation Maximization [58].

The approach of a modified intention-to-treat analysis will be used, which essentially means that to include patients in this study, patients in the intervention group need to receive an SMR after baseline questionnaires are completed, and patients in the control group need to complete baseline questionnaires after randomization.

Secondly, a sensitivity analysis will be performed to measure the effects of an SMR in patients in whom at least one medication regimen change was implemented or to whom at least one recommendation has been given.

Data will be analyzed using SPSS version 24. P-values ≤ 0.05 are regarded as statistically significant. Data concerning the semi-structured interviews will be imported in and analyzed with Atlas Ti version 8.

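### With the stated SD of 15, 198 patients do not give 80% power for a clinically important difference: power is about 12% for the 1.6-point MID and about 46% for the expected 4 points

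*Protocol article*

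**What the plan says.** Section 2.4.1 (Primary outcome) of the protocol article gives 1.6 points on the PDQ-39 total score as the minimally important difference (MID). Section 2.5 (Sample size) repeats that "a difference of 1.6 points in the overall score of this questionnaire is considered as clinically relevant". It then introduces a larger figure: "a difference of four points in the total score is expected to appear after intervention". On variability it says "A standard deviation of 15 was found in previous research" and "This standard deviation is used to make a preliminary calculation of the sample size". From a 5% significance level and 80% power it concludes that "a sample size of 198 subjects, separated into two groups of 99, is required to detect a clinically important difference between both groups".

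The same section treats the calculation as provisional. It acknowledges that the SD and the effect are uncertain, and plans an interim analysis after 2 × 25 patients with 3 months of follow-up to set the final sample size. Section 2.7 (Data analysis) gives one decision threshold: "P-values ≤ 0.05 are regarded as statistically significant".

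**The concern.** The power statement does not say which difference it refers to. The nearest candidates are 1.6 points, the only figure for the total score that the article calls clinically relevant, and 4 points, which it calls expected. With the stated SD, 99 per group gives 80% power for neither.

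This matters most if the result is not significant. A reader who trusts an 80% power figure for a clinically important difference may take p > 0.05 as evidence that the medication review has no worthwhile effect on quality of life. At this size the confidence interval would usually be too wide to support that.

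**Working it through.** **Inputs.** MID 1.6 points (2.4.1 and 2.5); expected difference 4 points, SD 15, alpha 5%, power 80%, 99 per group (2.5); 1:1 allocation (2.2). The article does not state sidedness. Two-sided is assumed, and one-sided results are given as a check.

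**Reproducing 198.** For two independent means, n per group = 2 × (1.960 + 0.842)² × SD² / difference², where (1.960 + 0.842)² ≈ 7.849.

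- Difference 4, SD 15: 2 × 7.849 × 225 / 16 = 220.7, so 221 per group (442 in total; 444 with the t-test). One-sided: 174 per group.
- Difference 1.6, SD 15: 2 × 7.849 × 225 / 2.56 ≈ 1,380 per group.
- Difference 4, SD 10: 2 × 7.849 × 100 / 16 = 98.1, so 99 per group. This matches the plan.
- Difference 6, SD 15: also 99 per group, because 6/15 = 4/10 = 0.40.

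So 198 corresponds to a standardised difference of 0.40. The stated inputs give 4/15 = 0.27 for the expected effect and 1.6/15 = 0.11 for the MID.

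**Power at 99 per group.** SE = SD × √(2/99), and power ≈ Φ(difference/SE − 1.960).

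| SD | SE | Power for 1.6 | Power for 4 | Difference detectable with 80% power (2.80 × SE) |
|---|---|---|---|---|
| 15 | 2.132 | Φ(0.750 − 1.960) = 11.3% (t-test 11.6%) | Φ(1.876 − 1.960) = 46.7% (t-test 46.3%) | 6.0 points |
| 10 | 1.421 | Φ(1.126 − 1.960) = 20.2% (t-test 20.2%) | Φ(2.814 − 1.960) = 80.4% (t-test 80.0%) | 4.0 points |

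One-sided, power for 1.6 points is 19% (SD 15) or 30% (SD 10), and power for 4 points at SD 15 is 59%. Using 100 per group, the enrolment aim, changes nothing material: 11.7% and 46.7% at SD 15.

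**Correcting the 4-point calculation does not settle the MID.** In any two-sided 5% design with exactly 80% power for 4 points, the standardised distance for 1.6 points is 0.4 × 2.80 = 1.12. Then Φ(1.12 − 1.96) = Φ(−0.84) ≈ 20%, whatever the SD.

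**Effect of baseline adjustment.** The article gives no baseline correlation r, so the values here are assumptions. With an effective SD of 15 × √(1 − r²), r = 0.5 to 0.8 gives 14% to 24% power for 1.6 points and 58% to 88% for 4 points. An r of about 0.745 gives an effective SD of 10. Reaching 80% power for 1.6 points at 99 per group needs an effective SD of about 4, which from SD 15 means r of about 0.96.

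**Confidence interval.** The 95% half-width is about 4.2 points (SD 15) or 2.8 points (SD 10), which is 2.6 or 1.8 times the MID. An observed difference of zero leaves a 1.6-point improvement inside the interval. To exclude it, the observed result would have to favour usual care by more than about 4.2 − 1.6 = 2.6 points (SD 15) or 2.8 − 1.6 = 1.2 points (SD 10).

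**The case against.** A reader might infer that the plan claims 80% power for 1.6 points and so contradicts itself. The text does not go that far. It refers to a clinically important difference, not the minimal one; it discloses 4 points as the expected effect; and 4 points exceeds the threshold, so it is itself clinically important. Sizing a trial on an expected effect above the MID is a legitimate choice. This part of the objection stands: the phrase is ambiguous, not a strict contradiction. It does not rescue the power figure, because at SD 15 the 4-point reading also falls well short of 80%.

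The calculation is labelled preliminary and an interim re-estimation is planned. That stands as context: the final sample size may differ. It does not make 198 follow from the inputs given, and nothing in the section says the re-estimation will target 1.6 points.

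Section 2.7 plans a repeated-measurement analysis, which could reduce the effective SD. This is fair, and it limits another tempting reading, that an observed 1.6-point difference could never be significant. If an SD of 10 and a correlation of 0.8 are both assumed, the effective SD is 10 × √(1 − 0.64) = 6, power for 1.6 points is about 46%, and the smallest significant difference is about 1.7 points. However, the article states no correlation and says that the SD of 15 was the one used.

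Finally, nowhere does the article say that a non-significant result will be read as no relevant effect, and rules for interpreting the confidence interval are often left to the analysis plan. Their absence is not an error. The safeguard is recommended because the present power sentence invites that misreading.

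**Conclusion.** The point holds: the stated 80% power is not delivered on either natural reading of the sentence. With SD 15, 99 per group and a two-sided 5% test, power is about 12% for the 1.6-point MID and about 46% for the expected 4 points, and about 6 points are needed for 80%. If an SD of 10 was meant, 80% for 4 points is right and power for the MID is about 20%. No single SD supports both 80% for 4 points and 12% for 1.6 points, so each pair of figures must be quoted on its own SD.

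These results assume an unadjusted comparison of two means with no gain from baseline adjustment, and 99 per group before any re-estimation. Choosing 4 points as the target is not a fault. The faults are the unnamed target difference and a power figure that does not match the stated SD.

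**What to change.** In section 2.5, name the difference the trial is powered for, say that it is an expected effect above the MID if that is the intention, and reconcile difference, SD and sample size:

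- If 198 and SD 15 both stay, replace the 80% claim with about 46% power for 4 points and about 12% for 1.6 points.
- If SD 10 was meant, correct the SD and state 80% for 4 points and about 20% for 1.6 points.
- If SD 15 and 80% power for 4 points are both to stay, the size is about 442 in total, and power for 1.6 points is still about 20%.

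In each case, say that the figures are preliminary until the planned interim re-estimation. Rewording the sentence to claim 80% power for 4 points, with 198 patients and SD 15 left in place, would not do, because that statement would be false.

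In section 2.7, add that the primary between-group difference is reported with its 95% confidence interval and read against a 1.6-point improvement (a lower PDQ-39 score). A non-significant result whose interval still includes that improvement is called inconclusive.

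The first two options and the 2.7 addition need only wording, with no extra patients or data. The price is a less favourable stated power and a more cautious reading of a null result. The third option would more than double recruitment.

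### The stated sample size of 198 does not follow from the stated inputs: they need about 442, and 99 per group gives about 46% power, not 80%

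*Protocol article*

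**What the plan says.** All the ingredients are in section 2.5 (Sample size) of the protocol article.

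- Effect: "a difference of four points in the total score is expected to appear after intervention".
- Variability, and its role in the calculation: "A standard deviation of 15 was found in previous research [51]. This standard deviation is used to make a preliminary calculation of the sample size".
- Error rates: 5% significance and 80% power. Sidedness is not given there; section 2.7 (Data analysis) says only that "P-values ≤ 0.05 are regarded as statistically significant".
- Result: "a sample size of 198 subjects, separated into two groups of 99, is required".

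The abstract carries the figure forward as the recruitment target: "we aim to enroll 200 PD patients". Section 2.1 repeats it, and section 2.2 gives 1:1 allocation. Section 2.5 calls the calculation preliminary and plans an interim analysis after 25 patients per group have 3 months of follow-up, from which the final size will be set. It mentions no correlation between baseline and follow-up, no change-score SD and no covariate adjustment.

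**The concern.** The inputs and the result stand in the same paragraph, and they disagree. A 4-point difference with an SD of 15 is a standardised effect of 4/15 = 0.267. Two groups of 99 are what a standardised effect of 0.40 requires. The gap is far too large to be rounding.

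This is the headline power claim for the primary outcome. If the SD is 15 and the groups are compared without adjustment, the trial is slightly more likely to miss a true 4-point effect than to find it, while readers are told that the chance of finding it is 80%. A non-significant result would then be given more weight as evidence of no effect than it deserves. There is also a practical risk at the interim. If the data confirm the assumed SD and effect, a correct calculation would more than double the target, which nobody reading the article would expect. A repeat of the faulty calculation would leave the target where it is.

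**Working it through.** **Inputs.** Difference 4, SD 15, alpha 0.05, power 0.80 (section 2.5); 1:1 allocation (section 2.2). Two-sided testing is assumed, and one-sided testing is tried as well.

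**Attempt to reproduce the plan's figure.** For two means,

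n per group = 2 × (1.96 + 0.8416)² × SD² / difference²

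= 2 × 7.849 × 225 / 16 = 220.75, so 221 per group and 442 in total. The t-based solution is 221.7, so 222 per group and 444 in total. The plan states 99 and 198. The ratio is 442/198 = 2.2.

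**Other readings of the same inputs.**

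| Reading | n per group |
|---|---|
| Two-sided 5%, difference 4, SD 15 | 221 (t-based 222) |
| One-sided 5%, difference 4, SD 15 | 174 (t-based 175) |
| Difference 1.6 (the plan's minimally important difference), two-sided | 1,380 |
| Single-sample or paired formula, two-sided | 113 patients in all |
| Single-sample or paired formula, one-sided | 89 patients in all |

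None gives 99 per group or 198 in total. A Mann-Whitney allowance would only raise the number.

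**What does give 99.**

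- SD 10, difference 4: 2 × 7.849 × 100 / 16 = 98.1, so 99.
- SD 15, difference 6: 2 × 7.849 × 225 / 36 = 98.1, so 99.

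Both are a standardised effect of 0.40. By the t distribution the requirement is 99.08, and 99 per group gives 79.97% power, so the match does not depend on the formula in any way that matters.

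**Power with 99 per group at SD 15.**

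- Standard error = 15 × √(2/99) = 2.132.
- Normal approximation: Φ(4/2.132 − 1.96) = Φ(−0.084) = 46.7%.
- t-test: 46.3% two-sided, 58.9% one-sided.
- With 100 per group, the recruitment target: 47.0% (normal approximation, two-sided).
- Smallest observed difference reaching the 5% level, two-sided: about 1.97 × 2.132 = 4.20 points. An observed difference of exactly 4 would not be significant.
- Difference detectable with 80% power: 6.0 points.

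**Correlation r that would justify 99 per group at SD 15.** The variance must shrink to 99/220.75 = 0.448 of its value.

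- Baseline-adjusted, one follow-up: 1 − r² = 0.448, so r = 0.74.
- Change from baseline: 2(1 − r) = 0.448, so r = 0.78.
- Baseline-adjusted mean of both follow-ups, assuming equal correlations among the three visits: (1 + r)/2 − r² = 0.448, so r is about 0.59. At r = 0.5 the power is about 75%.

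**The case against.** Three arguments can be made for the plan.

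First, the 46% belongs to an unadjusted comparison at one time point. Outcomes are measured at baseline, 3 and 6 months, and section 2.7 plans a repeated measurement analysis for continuous variables. The power of that analysis depends on a correlation the article does not give, so it is unknown rather than shown to be 46%. This stands as a qualification: the 46% and the 4.20-point threshold must be labelled as unadjusted. It does not rescue the printed figure. Section 2.5 says the SD of 15 is what entered the calculation, and section 2.7 gives missing data as the reason for the repeated measurement analysis, not a gain in precision.

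Second, the calculation is called preliminary and the final size is to be set at the interim. That makes 198 provisional and limits the damage if the later calculation is done correctly. But the interim is justified by doubt about the SD and the effect. It does not make the present arithmetic right.

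Third, a journal article condenses a longer protocol, so adjustment details may be given there. That would excuse an omission. It does not excuse printed inputs that contradict the printed result.

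Powering for an expected 4 points when 1.6 points is already considered relevant is a legitimate design choice. It forms no part of this finding.

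**Conclusion.** The concern holds. On the inputs printed in section 2.5, the required size is 221 to 222 per group (442 to 444 in total), not 99 (198). Two groups of 99 give about 46% power for 4 points in a two-sided unadjusted comparison at SD 15, or about 59% one-sided. The 80% claim is true for 6 points at SD 15, or for 4 points at SD 10. It could also be true for 4 points at SD 15 with baseline adjustment, given a correlation between about 0.59 and 0.78 depending on the analysis. The article states none of these. The recomputation assumes only equal groups and a common SD, and the conclusion is the same for one-sided or two-sided testing and for the normal or t-based formula. It must be fixed, because it is the stated power for the primary outcome.

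**What to change.** Find out which inputs produced 99 per group, then rewrite section 2.5 so that inputs, size and power agree. One of the following should be chosen:

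1. **SD 10 was used.** State it, justify it for this population, and remove the statement that 15 was used.
2. **The calculation relied on baseline or repeated measurements.** Name the analysis and time point, state the assumed correlation with its source, and show power over a range of correlations.
3. **SD 15 and 198 patients are kept without adjustment.** State the power as 46% for 4 points, with 80% reached at 6 points.
4. **SD 15, 4 points and 80% power are kept without adjustment.** Change the total to 442 (444 t-based), and the target in the abstract and section 2.1 with it.

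In every case, state the sidedness and use the corrected calculation for the interim re-estimation.

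Options 1 to 3 cost only wording and, under option 3, a much less favourable power statement. Option 4 costs 442 − 198 = 244 further patients (246 t-based).

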### Safety reporting

2.6

All adverse events, defined as any undesirable experience occurring to a subject during the study, whether or not considered related to the experimental intervention, reported spontaneously by the subject or observed by the investigator or staff, will be recorded. Serious adverse events (SAEs) which are likely to be associated with the study intervention will be reported within 7 days after the responsible investigator has first knowledge of it. Due to the disease status and the advanced age of patients with PD included in this study, expected SAEs such as hospitalization and death may occur. Unlikely is that these SAEs are associated with participation in the study. To cover this, a six-monthly line listing will be provided to the Medical Ethical Review Board Twente. An annual safety report will be submitted to the accredited METC as well. A Data and Safety Monitoring Board was not installed.

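### The enrolment target of 200 is the complete-data sample size of 198 with a 1% margin, so the stated 80% power makes no allowance for loss, on top of a required number that does not follow from its own inputs

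*Protocol article*

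**What the plan says.** Section 2.5 (Sample size) takes a between-group difference of four points on the PDQ-39 total score ("a difference of four points in the total score is expected to appear after intervention") and an SD of 15 from previous research. "Based on a significance of 5% and a power of 80" per cent, it concludes that "a sample size of 198 subjects, separated into two groups of 99, is required". It calls the calculation preliminary. An interim analysis after 2 × 25 patients with 3 months of follow-up is to inform the final number. The reasons given are that the SD may differ and that the effect of a medication review is unknown; loss to follow-up is not among them.

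Section 2.1 (Design) gives the target: "We aim to enroll 200 patients with idiopathic PD". Follow-up questionnaires are due at 3 and 6 months.

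Section 2.6 (Safety reporting) notes, in view of disease status and age, that "expected SAEs such as hospitalization and death may occur". Section 2.7 (Data analysis) says that "a repeated measurement analysis will be performed to deal with possible missing data" and adds Expectation Maximization imputation following the PDQ-39 manual. Section 2.2 counts an intervention patient as definitely included only after baseline measurements and the medication review; a control patient needs baseline measurements only.

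The article states no loss rate, and neither section 2.1 nor section 2.5 says which follow-up visit the sample size refers to.

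**The concern.** A two-group calculation of this kind gives the number of patients who contribute an outcome. Here that number serves, almost unchanged, as the number to enrol. If more than two of 200 included patients return no follow-up PDQ-39, the number that the plan itself calls required is missed. An elderly group with a progressive disease, followed for six months by questionnaire, is unlikely to stay within that margin, and the plan's own provisions for deaths and missing data allow for this.

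At stake is how a neutral result would be read. Someone who takes the 80% at face value would give a non-significant result more weight than the design supports. The omission could also pass into the final sample size, because the reasons given for re-estimation do not include loss.

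**Working it through.** **Inputs.** Difference 4, SD 15, significance 5%, power 80%, 99 per group (section 2.5); 1:1 allocation (section 2.2); 200 enrolled (section 2.1). The test is taken as two-sided, which the article does not state. The loss rates are assumptions, since the documents give none.

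**Step 1: the margin.** 200 − 198 = 2, and 2/200 = 1.0%.

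**Step 2: can 198 be reproduced?** With n per group = 2(z₀.₉₇₅ + z₀.₈₀)² × SD²/difference²:

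- (1.960 + 0.842)² = 7.849 before rounding of the z-values.
- Stated inputs: 2 × 7.849 × 225/16 = 220.7, so 221 per group (442 in total). The t-test version gives 222 per group.
- A one-sided test gives 174 per group (175 by t-test), so sidedness does not explain 99.
- SD 10 with difference 4: 2 × 7.849 × 100/16 = 98.1, so 99 per group. SD 15 with difference 6 has the same ratio (0.40) and also gives 99.
- SD 15 with a baseline correlation of about 0.74 (covariance adjustment) or 0.78 (change scores) would also give 99, but no correlation is stated.

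So 198 does not follow from the stated inputs. It fits a standardised effect of 0.40, whereas section 2.5 gives 4/15 = 0.27.

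**Step 3: power for 200 enrolled at each assumed loss.** Two-sample t-test, two-sided 5%, n per group = 100 × (1 − loss). A lost patient is taken to have no follow-up PDQ-39.

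| Loss | n per group | Stated inputs (4/15) | If the effect were 0.40 |
|---|---|---|---|
| 1% | 99 | 46.3% | 80.0% |
| 5% | 95 | 44.8% | 78.3% |
| 10% | 90 | 42.8% | 76.1% |
| 20% | 80 | 38.8% | 71.0% |

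The normal approximation gives values within about 0.6 of a percentage point of these (for example 46.7% at 99 and 43.2% at 90 per group).

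**Step 4: how much is due to loss?** On the stated inputs, the gap from 80% to 46.3% is about 34 points with 99 per group complete. Going from 99 to 90 per group costs a further 3.5 points (46.3 − 42.8), and to 80 per group 7.5 points (46.3 − 38.8). At an effect of 0.40 the corresponding costs are about 4 and 9 points.

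**Step 5: does correcting the inputs remove the problem?** No. If 442 were adopted as the analysed number, an assumed 10% loss would mean 442/0.90 = 491.1, or 492 for equal groups. Conversely, allowing for loss on top of 198 (198/0.90 = 220 enrolled) only brings back 99 per group, which is about 46% power on the stated inputs. The two corrections are separate.

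**The case against.** The strongest reply is that the shortfall in power is not caused by loss. On the plan's own inputs the 80% is missed with every patient complete. That stands. A reader might infer from the 1% margin that attrition is why 80% is not reached, or that power falls from 80% to 76% at 10% loss. The documents support neither: the second figure needs an effect of 0.40 that appears nowhere in them.

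A reader might also infer that substantial attrition is predicted. Section 2.6 says only that deaths and hospitalisations may occur, section 2.7 calls missing data possible, and no rate is given. The loss rates used here are illustrations.

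There are mitigating features. An intervention patient lost before the medication review does not use up the target. Repeated-measures analysis keeps patients who return month 3 but not month 6, so the table overstates the cost for them. Neither helps with a patient who is included and returns no follow-up PDQ-39, and Expectation Maximization does not create information on the treatment effect for such a patient.

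The calculation is labelled preliminary, and the interim will show loss up to 3 months. It would go too far to say that the re-estimation must repeat the omission, since no formula is given. What stands is that loss is not among the stated reasons for revising N, and that a look defined by 3 months of follow-up gives little information on loss between months 3 and 6.

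Finally, a condensed article may leave an attrition allowance to the full protocol. Here, however, it prints both the number required and the number to be enrolled, and between those two figures there is room for 1% and no more.

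**Conclusion.** The point holds as a secondary defect of section 2.5. The stated 80% power is a complete-data figure, and 200 enrolled leaves a 1% margin for everything lost after inclusion. The larger defect is that 198 does not follow from a difference of 4 and an SD of 15, which give about 46% power at 99 per group with no loss. On those inputs, power for 200 enrolled is about 45%, 43% and 39% at 5%, 10% and 20% complete loss. The figures of about 78%, 76% and 71% apply only if an effect of 0.40 can be documented.

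These results assume a two-sided t-test, assumed loss rates spread equally over the groups, and no contribution from lost patients; partial follow-up would soften them. The omission should be corrected together with the inputs, because neither correction makes the other unnecessary.

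**What to change.** In section 2.5, when the inputs are corrected or the source of 198 is documented:

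1. State that the calculated N is the number of patients with an analysed follow-up PDQ-39, and name the time point (3 or 6 months) to which it refers.
2. State the assumed loss to that time point.
3. Restate the power, or the detectable difference, for 200 enrolled at that loss. Do not print 76% as the replacement for 80% unless inputs giving a standardised effect of 0.40 are documented; on the present inputs the value at 10% loss is about 43%.
4. In the interim re-estimation, set enrolled N = analysed N/(1 − anticipated loss to the named time point), with the anticipated loss informed by what is observed at 3 months.

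The cost is a few sentences, one term in the re-estimation and a less favourable stated power. This fix requires no additional patients: it makes the stated power match the enrolment target. Whether to enlarge the trial is a separate decision, which depends on the corrected inputs.
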